### Statistical analysis

Baseline characteristics of the study population will be presented as counts and percents for categorical variables and as mean ± SD for continuous variables. Kappa statistic will be calculated to determine interobserver agreement. The number of lesions in our population of patients recruited will be estimated by the adjusted Wald interval at 95% in accordance with the method recommended by Agresti & Coull [20]. With small sample sizes, as recommended we will use the mid-point of the adjusted Wald interval instead of the observed proportion [21]. The statistical analyses will be performed using SPSS 10.0.7 software (Chicago, IL, USA). The compound score for global cognitive function will be constructed by calculating the average of the z scores for all the above tests. Cognitive decline will be calculated by subtracting the z scores for memory performance, psychomotor speed, and global cognitive function at follow-up from the z scores at base line. All analyses will be adjusted for age, sex, and level of education, as well as the interval between the two sets of neuropsychological tests.

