**Study design:**

This prospective study will be performed in patients with severe aortic valve stenosis. To assess the occurrence of cerebral infarction, all patients will undergo cerebral DW-MRI and neurological assessment within 24 hours before, and 48 hours after cardiac catheterization and retrograde catheterization of the aortic valve. Randomization for the access site will be performed before coronary angiography. A subgroup will be monitored by transcranial power M-mode Doppler during cardiac catheterization to observe cerebral blood flow and track emboli. Neuropsychological tests will also be recorded in a subgroup of patients before and after the interventional procedures to assess the impact of silent brain injury on potential cognitive decline. The primary end-point of the study is a direct comparison of ischemic cerebral lesions as detected by serial cerebral DW-MRI between patients explored by radial access and patients explored by femoral access. Secondary end-points include comparison of neuropsychological test performance and number of microembolism signals observed in the two groups.

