## Design and methods

### Study design

Prospective multicenter randomized trial (4 centers currently involved: 2 in France, 1 in Italy and 1 in Austria).

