### Neuropsychological assessment

Patients will undergo neuropsychological assessment within 24 hours before, and 48 hours after, cardiac catheterization. All patients with documented cerebral infarction at DW-MRI will be asked to come back for a new neuropsychological assessment at 1 year follow-up.

The aim of the cognitive testing is to provide clinical evidence of potential cerebral damage after cardiac catheterization and to quantify this potential cognitive decline allowing comparison of two groups of patients explored either by radial or femoral approaches. The tests must be sensitive enough to detect potential post-procedure cognitive decline and also able to explore different brain areas. Most of the neuropsychological tests that will be administered have been reported to be sensitive to change after CABG or PCI procedures [19] and will include: Digit Span Forwards and Backwards, Trail making test A and B, Wechsler Memory Scale visual reproduction test, Rey-Osterrieth's figure test, Grober-Buschckle's test, Rey Auditory Verbal Learning Test, Verbal fluency test, and Confrontation naming test.

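### The cognitive models adjust for age, sex, education and test interval but not for centre or language, so the non-randomised infarct contrast can be confounded if retest gain and lesion rates both differ by centre (low severity, secondary end-point)

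*Protocol article*

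**What the plan says.** Four statements in the protocol article bear on this.

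- **Setting** (Study design): "4 centers currently involved: 2 in France, 1 in Italy and 1 in Austria".
- **Who is tested** (abstract, Study design): "Neuropsychological tests will also be recorded in a subgroup of patients before and after the interventional procedures". The centres that supply this subgroup are not named.
- **Battery** (Neuropsychological assessment): "Digit Span Forwards and Backwards, Trail making test A and B, Wechsler Memory Scale visual reproduction test, Rey-Osterrieth's figure test", then a second verbal learning test, and "Rey Auditory Verbal Learning Test, Verbal fluency test, and Confrontation naming test". Testing is planned no more than a day before catheterization and again no more than two days after it.
- **Score and model** (Statistical analysis): "The compound score for global cognitive function will be constructed by calculating the average of the z scores for all the above tests". Decline is formed by subtracting the z scores "at follow-up from the z scores at base line". Then: "All analyses will be adjusted for age, sex, and level of education, as well as the interval between the two sets of neuropsychological tests".

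The reference mean and SD behind the z scores are not given. The effect of silent infarction on cognition is a secondary end-point and the third study objective.

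**The concern.** The adjustment list is stated explicitly, and centre, country and language are not on it. That makes it a model choice that can be examined, not a detail left open.

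Patients with and without a new lesion are not allocated at random, so nothing balances centre between them. The Discussion says that procedure length or fluoroscopy time appear to be the only factors independently associated with infarction. Both can plausibly vary by operator and centre, and lesion rates could vary with them.

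The two test sessions are at most about three days apart, so practice gain may be a sizeable part of the measured change. Word lists, fluency letters and naming items differ between French, Italian and German versions, and the gain on retest may differ too. The test-interval covariate does not capture that.

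If both conditions hold, part of a centre difference would be read as an effect of infarction, or would hide one.

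**Working it through.** **The plan's own figure.** The article gives no figure for the cognitive analysis. Its sample size of 152 is for the DW-MRI end-point and is not in question here. Its planned rates do give an overall lesion rate for anchoring: with 1:1 allocation, (5.9% + 23%)/2 = 14.45%.

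**Step 1: count the scores.** Splitting Digit Span and Trail Making into two parts each gives ten scores. Four are strongly language-bound: the two verbal learning tests, fluency and naming. Counting both Digit Span parts as verbal makes six. The two Trail Making parts, visual reproduction and the complex figure are non-verbal.

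**Step 2: what cancels.** Let a version add a constant c to a score at both visits. Then decline = (z_base + c) − (z_fu + c) = z_base − z_fu, and c drops out. If a version instead has its own retest gain g, then decline = z_base − (z_fu + g), and g stays in.

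**Step 3: size of the confounding, per affected score.** All inputs here are assumptions; the article gives no centre mix, lesion rates by centre or cognitive SDs. Patient shares by language are 0.50/0.25/0.25, lesion rates 8%/14%/28%, and retest gains g, g/2 and 0.

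- Overall lesion rate: 0.040 + 0.035 + 0.070 = 0.145, in line with the 14.45% above.
- Mean gain with infarct: (0.040g + 0.035 × g/2)/0.145 = 0.0575g/0.145 = 0.397g.
- Mean gain without infarct: (0.460g + 0.215 × g/2)/0.855 = 0.5675g/0.855 = 0.664g.
- Difference: 0.267g, that is 0.080 SD at g = 0.3 and 0.134 SD at g = 0.5.

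**Step 4: size on the composite.** The composite is an unweighted mean of ten scores, so only the affected share carries the difference.

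| Affected scores | g = 0.3 | g = 0.5 |
|---|---|---|
| 6 of 10 | 0.6 × 0.080 = 0.048 | 0.6 × 0.134 = 0.080 |
| 4 of 10 | 0.4 × 0.080 = 0.032 | 0.4 × 0.134 = 0.054 |

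The range is about 0.03 to 0.08 z.

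**Step 5: simulation.** Each scenario used 2,000 trials with all 152 patients tested, language shares of 50/25/25%, six of ten scores affected and no true infarct effect. Baseline levels differed by 0/+0.5/−0.5 SD between versions. The adjusted model added a language factor.

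| Scenario | Bias, no term | Type I error, no term | Bias, with term | Type I error, with term |
|---|---|---|---|---|
| Level shift only; lesion rates 8/25/15% | −0.002 | 4.0% | −0.002 | 4.2% |
| Plus 0.3 SD gain in the second language; rates 8/25/15% | −0.041 | 9.9% | −0.001 | 4.5% |
| Same gain; equal rates of 14.5% | −0.002 | 4.9% | −0.003 | 4.8% |

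A hand check of the middle row: the overall rate is 0.040 + 0.0625 + 0.0375 = 0.14. The second language's share is 0.0625/0.14 = 0.446 among infarcts and 0.1875/0.86 = 0.218 among the rest. Then 0.6 × 0.3 × (0.446 − 0.218) = 0.041. The sign is negative because here the higher gain goes with the higher lesion rate, so infarct patients seem to decline less. In Step 3 the order is reversed and the artefact looks like harm.

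**The case against.** The strongest counter-argument is that the bias needs several things at once: more than one language in the tested subgroup, version-specific retest gain, and lesion rates that differ in step with it. No figure in the article supports the size of any of these. The assumed 28% in one country exceeds even the planned femoral rate of 23%, and with equal lesion rates the simulated bias vanishes. An article also condenses a fuller protocol, which may handle centre. This stands as a reason for low severity. It does not remove the point, because the published list claims to cover all analyses and leaves out an obvious potential confounder of an observational contrast.

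The type I error of 9.9% also depends on the simulation's settings. It tests all 152 patients, whereas the article tests a subgroup, and it uses independent error of SD 0.7 per score and visit. That gives a composite change SD of only about √(2 × 0.49/10) = 0.31. With fewer patients or noisier change scores the same bias would inflate the error rate less.

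A reader might go further in three ways that the documents do not support.

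- **That any difference between test versions distorts the infarct contrast.** Level differences cancel in the decline score (Step 2, first simulation row). They would matter only in an analysis of a single visit.
- **That z scores pooled over countries inflate the SD and shrink verbal losses.** The article does not say whether the reference is pooled, per centre or normative, nor which centres do the testing, so pooling is an inference.
- **That the radial-femoral comparison is biased.** It is randomised, so unbiased in expectation.

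**Conclusion.** The point holds in a narrow form. Leaving centre and language out of the adjustment list exposes one secondary analysis, infarct versus no infarct on cognitive decline, to confounding by centre. Two conditions must hold together: retest gain that differs by version, and lesion rates that differ by centre. Under the assumed values the spurious composite difference is about 0.03 to 0.08 z, and it can go in either direction. In the simulated case type I error is 9.9% without a language term and 4.5% with it. All of these sizes rest on assumed centre shares, lesion rates and retest gains. Severity is low: the primary DW-MRI comparison is untouched and the randomised arm contrast on cognition is not biased in expectation.

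**What to change.** In the Statistical analysis section, add centre as a factor to the adjustment list for the cognitive models. Language would also serve, with the two French centres taken together. The cost is three degrees of freedom for four centres or two for three languages, plus a wording change.

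If a single centre or a single language supplies the cognitive subgroup, say so; the term is then unnecessary.

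Standardising each test within its language version is not recommended. With 25% of 152 patients, a smaller language group has at most 38. The relative standard error of its SD is about 1/√(2 × 37) = 12%. That compares with an inflation of √(1 + 0.5 × 0.5²) − 1 = 6% that it would remove if the SD were pooled and version means differed by ±0.5 SD.

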### End points

#### (i) Primary end-point

Number of patients observed with new cerebral lesions either symptomatic or not after cardiac catheterization as detected by DW-MRI in each group (comparison of radial and femoral access).

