### Sample size calculation

Based on a pilot study [6] we think that radial approach will be associated with a median rate of 5.9% [0.01–12.5;95%CI] of new lesions as detected by cerebral DW-MRI. In patients with aortic stenosis explored by femoral approach we expect a 23% [15–31;95%CI] rate of similar events [3]. With randomization 1:1 an alpha risk of 5% and beta risk of 20% we anticipate a sample size population of 152 patients needed to demonstrate that radial approach could be associated with better outcome concerning the occurrence of silent cerebral infarctions (76 patients in each arm of the study).

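### The cognitive arm comparison uses a change score adjusted for age, sex, education and test interval but not for the baseline score, which gives up precision at no benefit

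*Protocol article*

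**What the plan says.** All references are to the protocol article.

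- **Outcome (Statistical analysis).** The cognitive outcome is a simple difference: "Cognitive decline will be calculated by subtracting the z scores for memory performance, psychomotor speed, and global cognitive function at follow-up", the subtraction being from the baseline values. A positive value therefore means decline.
- **Covariates (Statistical analysis).** The next sentence reads: "All analyses will be adjusted for age, sex, and level of education, as well as the interval between the two sets of neuropsychological tests". The baseline score is not named.
- **Purpose (Neuropsychological assessment).** Testing is meant to "quantify this potential cognitive decline allowing comparison of two groups of patients explored either by radial or femoral approaches". The abstract also lists a between-group comparison of test performance as a secondary end-point. This is a contrast between randomised arms.
- **A second cognitive question (Study objectives; Secondary end-points).** The article also asks whether silent infarction affects cognition. That contrast is not randomised.
- **Who is tested.** The abstract says: "Neuropsychological tests will also be recorded in a subgroup of patients before and after the interventional procedures". The Neuropsychological assessment section speaks of patients without that limit. Neither place gives a number.

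**The concern.** In a randomised comparison of a score measured before and after the procedure, the baseline value usually predicts the later value better than age, sex or education does. Subtracting it forces its coefficient to be exactly 1. Estimating the coefficient instead gives an arm contrast with the same expectation and, apart from one degree of freedom, a variance that is never larger. The article names its covariates and leaves this one out.

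What is at stake is the precision of a secondary comparison for which the article states no sample size calculation. Its validity is not in question.

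**Working it through.** **The article's own figure.** The only sample size given is for the primary end-point. The inputs are "radial approach will be associated with a median rate of 5.9"% and "explored by femoral approach we expect a 23"%, with alpha 5%, power 80% and 1:1 allocation, leading to 76 per arm and 152 in all.

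- Difference: 0.23 − 0.059 = 0.171. Mean rate: 0.1445.
- Two-sided, uncorrected: n = [1.96·√(2·0.1445·0.8555) + 0.842·√(0.23·0.77 + 0.059·0.941)]² / 0.171² ≈ 65.2, so 66 per arm.
- With continuity correction: (65.2/4)·[1 + √(1 + 4/(65.2·0.171))]² ≈ 76.4, so 77 per arm and 154 in all.

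This is within 2 patients of 152. The figure is thus consistent with an unadjusted comparison of two proportions. That bears on how far the covariate sentence reaches. It does not size the cognitive comparison.

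**Cognitive arm comparison.** Let s0 and s1 be the SDs at baseline and follow-up and r their correlation. Per patient, the variance that drives the arm contrast is:

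- change score: s0² + s1² − 2·r·s0·s1
- adjusted for baseline: s1²·(1 − r²)
- change score minus adjusted: (s0 − r·s1)², which is never negative

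With s0 = s1 = 1 these become 2(1 − r) and 1 − r², and the ratio of adjusted to change-score variance is (1 + r)/2.

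The documents give no r, so a range is assumed. The last two columns show the difference detectable with 80% power at two-sided 5%, (1.96 + 0.842)·√(2V/76), where V is the variance in the second or third column. They suppose that all 76 patients per arm are tested, which is an upper bound.

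| r (assumed) | Change-score variance | Adjusted variance | Ratio | Excess SE of change score | Detectable, change score (SD) | Detectable, adjusted (SD) |
|---|---|---|---|---|---|---|
| 0.5 | 1.00 | 0.75 | 0.75 | 15.5% | 0.454 | 0.394 |
| 0.7 | 0.60 | 0.51 | 0.85 | 8.5% | 0.352 | 0.325 |
| 0.8 | 0.40 | 0.36 | 0.90 | 5.4% | 0.287 | 0.273 |
| 0.9 | 0.20 | 0.19 | 0.95 | 2.6% | 0.203 | 0.198 |

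With fewer patients tested, both detectable differences grow by the same factor and the ratio is unchanged.

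**Effect of the covariates already named.** With age, sex and education in both models, the r that matters is the partial correlation, which is usually lower than the raw one. As an illustration, suppose r = 0.8 and the covariates account for the same 30% of both scores. The partial r is then (0.8 − 0.3)/(1 − 0.3) = 0.71 and the ratio is 0.86, against 0.90 without the covariates. On these assumptions the existing covariates do not make baseline adjustment redundant.

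**The case against.** **The change score is valid.** Under randomisation it is unbiased for the arm difference. A reader might infer that regression to the mean distorts the result, but it acts on both arms equally in expectation. This objection stands, and only efficiency is left.

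**The list may not be exhaustive.** The article names adjusters without saying that there are no others, and the full analysis plan is not shown. Regressing the change score on arm and baseline gives the same arm estimate as regressing the follow-up score on them, apart from sign. Adding baseline would therefore not contradict the text. That makes the repair easy. The article nevertheless goes as far as defining the outcome and naming the covariates, and baseline is not one of them.

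**The gain may be small.** At r = 0.9 the standard error falls by under 3%. This stands, and the size remains an assumption.

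**The primary end-point.** A reader might infer from the opening words of the covariate sentence that the DW-MRI comparison ("Number of patients observed with new cerebral lesions either symptomatic or not after cardiac catheterization as detected by DW-MRI in each group") must also be adjusted for test interval, and would lose every patient without cognitive tests. The documents do not support this:

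- The sentence directly follows two sentences on cognitive scoring, and one of its covariates belongs to cognitive testing.
- Lesion frequency is dealt with earlier in the same section by an interval for a proportion.
- The sample size section mentions no covariates.
- The abstract and the Neuropsychological assessment section differ on whether only a subgroup is tested, so it is not established that any patient would be untested by design.

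What remains is a loose phrase.

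**The test interval.** One might object to this covariate as being fixed only after randomisation. If it hardly varies around the 48-hour test, including it does little harm. The 1-year visit for patients with infarction gives a reason for mentioning it.

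**Conclusion.** The point holds as a modest, avoidable loss of precision in the randomised radial versus femoral comparison of cognitive change. Adjusting for baseline brings the variance to 0.75 to 0.95 of the change-score variance for r from 0.5 to 0.9. This assumes equal SDs at the two assessments; the direction of the result does not need that assumption. No r is given in the documents.

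The result does not carry over to patients with versus without new lesions. Lesion status is not randomised, and there the choice between a change score and baseline adjustment alters what is estimated and can affect bias. Nor do the documents support describing the tested group as small, since they give no size for it. The scope of the covariate sentence is a wording matter only.

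**What to change.** In the Statistical analysis section, add the baseline z score of the same domain (memory, psychomotor speed or global function) as a covariate in the cognitive comparison of the two access arms, and keep age, sex and education. This can be written as ANCOVA on the follow-up z score or, equivalently, as the change score adjusted for baseline.

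As a minor clarification, open the covariate sentence with *All cognitive analyses*, so that the primary DW-MRI comparison cannot be read as depending on a test-interval variable.

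The cost is two changes of wording. Baseline scores are already collected, and neither the sample size nor the conduct of the trial changes.

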## Background

Acute cerebral infarction following cardiac catheterization is rare [1-3], but silent brain injury could occur at an unexpectedly high rate [3-6] as detected by diffusion-weighted (DW) magnetic resonance imaging (MRI). Indeed the high sensitivity of DW-MRI suggests that this technique could allow an improved estimate of cerebral ischemic events associated with cardiovascular catheterization procedures and could be used therefore as a surrogate endpoint for risk assessment of stroke [7]. The use of transcranial Doppler (TCD) sonography allows the recording of microemboli entering the middle cerebral artery during various endovascular interventions, including cardiac catheterization [8,9]. In the case of coronary bypass surgery, evidence indicates that microembolism might be related to cognitive impairment, based on the results of neuropsychological testing [10]. During cardiac catheterization, cerebral microembolism as detected by TCD has frequently been observed, but whether it is clinically relevant remains unknown [8,9]. However, recent studies mentioned above, have suggested that some of these microemboli could be related to silent cerebral embolisms responsible for acute ischemic brain injury, as documented by DW-MRI [3-6]. Furthermore there is increasing evidence that cumulative burden of ischemic brain injury causes neuropsychological deficits or aggravates vascular dementia [11]. Thus DW-MRI emerges as a valuable diagnostic method for the monitoring of periprocedural ischemic events in the brain and could be considered as a surrogate parameter for optimising diagnostic and therapeutic vascular interventions.

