#### (ii) Secondary end-points

Impact of potential silent cerebral infarction on cognitive impairement.

Number of microembolism signals observed at TCD between the two groups.

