### Cardiac catheterization

All patients will be examined clinically by a senior physician and assessed for any history of previous cerebral embolism. Transthoracic echocardiography, 12-lead surface electrocardiogram, and coronary angiography will be performed for all patients. Cardiac catheterizations will be undertaken by expert interventional cardiologists using a standard Seldinger technique using 5 French (F) catheters either by TRA or TFA according to randomization assignment. Sheaths will be removed immediately after the procedure in all patients. Unfractionated heparin (50 iu/kg) will be given intravenously to all patients at the beginning of the procedure. Retrograde catheterization of aortic valve will be attempted in a right oblique projection using a long exchange guidewire (0.035 inch, 260 cm length to ensure exchange of the pigtail catheter) using a left amplatz 1 catheter or a right Judkins catheter [15]. During attempts to cross the aortic valve, the wire will be regularly withdrawn and cleaned and the catheter flushed every 2 minutes according to Grossman's recommendations [16]. When the pigtail catheter is placed in the left ventricle, the wire will be withdrawn and the catheter vigorously aspirated and pressure measurements performed. After left ventriculography, the catheter will be rapidly withdrawn from the left ventricle into the ascending aorta with simultaneous pressure measurements. Maximum and mean pressure gradients will be established. The duration of the whole procedure and fluoroscopic time in all patients will also be recorded.

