### Magnetic resonance imaging

MRI will be done within 24 hours before, and 48 hours after, cardiac catheterization. MRI will be performed with a 1.5 Tesla system. The imaging protocol will include a DW single-shot spin echo echoplanar sequence acquired in the Anterior Commissure-Posterior Commissure plane with 24 contiguous sections (diffusion gradient b values of 0 and 1000 s/mm^2^, repetition time TR 6000 ms, echo time TE 120 ms, slice thickness 6 mm with no gap, matrix of 128 × 128 pixels, and field of view of 240 mm); fluid attenuated inversion recovery (FLAIR; TR/TE 10000/160 ms, TI 2200 ms); and T2-weighted turbo spin echo sequences (TR/TE 3500/94 ms). For DW-MRI, the diffusion gradients will be successively and separately applied in three orthogonal directions for a total acquisition time of 24 seconds. Trace images will then be generated and apparent diffusion coefficient (ADC) maps calculated with a dedicated software tool available on all recent MRI machines. The image analysis will be performed independently by two experienced neuroradiologists who will be blinded to the clinical data and will be unaware of the technical aspects of the angiographic cardiac procedure. For analysis of DW-MRI, the neuroradiologists will be asked to determine the presence, size, number, and vascular distribution of any focal diffusion abnormalities (bright lesions) in a pattern consistent with embolic lesions. Typical positive DW-MRI showing bright lesions (cerebral infarct) in asymptomatic patients are shown in Figures 1 and 2.

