**Figure 1 F1:**
[figure not shown]
Typical positive DW-MRI (diffusion weighted-MRI) in asymptomatic patient confirming a recent cerebral infarction before catheterization.

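### The covariate list for silent infarction and cognition omits pre-existing brain lesions; confounding is possible but small, and one baseline covariate would guard against it

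*Protocol article*

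**What the plan says.** The Statistical analysis section gives one adjustment set: "All analyses will be adjusted for age, sex, and level of education, as well as the interval between the two sets of neuropsychological tests". It defines the cognitive outcome as a difference from the patient's own starting value: "Cognitive decline will be calculated by subtracting the z scores for memory performance, psychomotor speed, and global cognitive function at follow-up from the z scores". The last-named scores are the baseline ones.

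The third study objective concerns what silent infarction means for cognition, and the first secondary end-point is "Impact of potential silent cerebral infarction on cognitive impairement".

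Several other places bear on prior lesions:

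- Background: "there is increasing evidence that cumulative burden of ischemic brain injury causes neuropsychological deficits or aggravates vascular dementia".
- Abstract, Study design: "all patients will undergo cerebral DW-MRI and neurological assessment within 24 hours before, and 48 hours after cardiac catheterization". The same paragraph limits neuropsychological testing to a subgroup.
- Magnetic resonance imaging: the sequences include "fluid attenuated inversion recovery (FLAIR; TR/TE 10000/160 ms, TI 2200 ms); and T2-weighted turbo spin echo sequences". The reading described covers focal diffusion abnormalities only.
- Cardiac catheterization: patients are "assessed for any history of previous cerebral embolism".
- Figure 1 shows an "asymptomatic patient confirming a recent cerebral infarction before catheterization".
- Study population: the only exclusions are a contraindication to MRI and inability to consent, so patients with earlier lesions can enter.

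**The concern.** Randomising the access site balances prior brain damage between the radial and femoral arms. It does not balance it between patients who develop a new lesion and those who do not. In that second contrast, the covariate list is the only protection against confounding. Vascular disease that left older lesions could plausibly also raise the risk of new ones, and the Background accepts that accumulated ischemic injury impairs cognition. If patients with old lesions also do worse between the two test sessions, part of that difference would be attributed to the new infarct. At stake is the interpretation of a secondary question. The primary end-point is not involved.

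**Working it through.** **The plan's own figure.** The Sample size calculation uses new-lesion rates of 5.9% (radial) and 23% (femoral), alpha 5%, power 80% and 1:1 allocation, and states 152 patients. A two-sided, continuity-corrected comparison of two proportions gives 77 per arm, or 154. That agrees closely, and the sample size is not in dispute. It is used here only for its rates.

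**Inputs from the protocol.**

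- Expected new infarcts: 76 × 0.059 + 76 × 0.23 = 4.5 + 17.5 ≈ 22 of 152.
- Overall rate: P = (0.059 + 0.23) / 2 = 0.1445.

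**Inputs that are assumed, because the documents give none.**

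- Prevalence of prior lesions, p: 20% to 40%.
- Odds ratio (OR) between prior lesion and new infarct: 1 to 3.
- Extra worsening of the change score in patients with prior lesions, g: 0 to 0.5 SD of the change score.

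**Formula.** With L denoting a prior lesion, and no true effect of the new infarct:

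spurious effect = g × [P(L | new infarct) − P(L | no new infarct)]

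The new-infarct rates without (a) and with (b) a prior lesion solve p·b + (1 − p)·a = P and b = OR·a / (1 − a + OR·a).

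**Worked case (p = 0.4, OR = 3, g = 0.5).**

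- Solving gives a ≈ 0.0893 and b ≈ 0.2272. Check: 0.4 × 0.2272 + 0.6 × 0.0893 = 0.1445.
- P(L | new infarct) = 0.4 × 0.2272 / 0.1445 = 0.629.
- P(L | no new infarct) = 0.4 × 0.7728 / 0.8555 = 0.361.
- Spurious effect = 0.5 × (0.629 − 0.361) = 0.134 SD.

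**Range.**

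| p | OR | L if new infarct | L if none | g = 0 | g = 0.2 | g = 0.5 |
|---|---|---|---|---|---|---|
| 0.2 | 1 | 0.200 | 0.200 | 0 | 0 | 0 |
| 0.2 | 2 | 0.308 | 0.182 | 0 | 0.025 | 0.063 |
| 0.2 | 3 | 0.380 | 0.170 | 0 | 0.042 | 0.105 |
| 0.4 | 1 | 0.400 | 0.400 | 0 | 0 | 0 |
| 0.4 | 2 | 0.546 | 0.375 | 0 | 0.034 | 0.085 |
| 0.4 | 3 | 0.629 | 0.361 | 0 | 0.054 | 0.134 |

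The spurious effect is zero whenever OR = 1 or g = 0.

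**Check by simulation.** A large simulated sample had OR 3, a fixed deficit of 0.5 score units in patients with prior lesions at both sessions, and age in the model. The false infarct effect was 0.00, 0.05 and 0.12 score units for g of 0, 0.2 and 0.5 score units. With a prior-lesion term added, it returned to about 0 each time. The fixed deficit alone produced no bias in the change score.

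**Against sampling error.** With 22 patients against 130, SE = √(1/22 + 1/130) = 0.23 SD. The largest spurious effect is 0.134 / 0.23 ≈ 0.6 SE. If only half the patients were tested (an assumed fraction, 11 against 65), SE = √(1/11 + 1/65) = 0.33 SD, and the ratio falls to about 0.4.

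**The case against.** The strongest case on the other side has four parts.

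1. **The contrast is not spelled out.** The only cognitive comparison the article describes in detail is radial against femoral, which is randomised. A model by infarct status may be left to fuller documents. This stands in part. The article does not describe the model, but it names the question as an objective and a secondary end-point, and its one stated adjustment set is said to apply to all analyses.

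2. **The change score removes the main route.** A reader might infer from the Background statement on cumulative burden that old damage will be counted as the effect of the new infarct. The documents do not support that. The Background speaks of deficits, meaning level, whereas the outcome is the difference between a test within 24 hours before and one 48 hours after the procedure. A stable deficit drops out. Age is already in the model and may absorb part of any remaining association. At one year only patients with infarction are recalled, so no contrast with lesion-free patients is described there.

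3. **The covariate does not yet exist.** A reader might infer that prior lesions are measured and then ignored. The images are acquired, but the described reading covers diffusion abnormalities only, so old infarcts on FLAIR/T2 would have to be scored. Figure 1 shows a recent lesion in one patient and gives no frequency for either recent or old lesions.

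4. **The effect is small and the model is small.** Every input to the size is assumed, the bias stays below one standard error, and testing in a subgroup limits how many terms the model can carry. This stands, and it argues for one compact covariate rather than several.

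**Conclusion.** The point holds as a minor one. The stated covariates leave out pre-existing lesions in a non-randomised analysis for which the protocol's own rationale makes them a candidate confounder. Confounding requires both an association between prior and new lesions and an effect of prior lesions on the change itself; the documents establish neither. Under the assumed ranges the spurious effect runs from 0 to about 0.13 SD. Sampling error is about 0.23 SD at best, and larger in a subgroup. It would be wrong to conclude that the planned analysis is biased by a known amount. It would equally be wrong to conclude that the trial's main result is at risk: the primary end-point, the radial-femoral cognitive comparison and the sample size are untouched.

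**What to change.** For the cognitive analysis of patients with against patients without a new lesion, and for that analysis only, add one yes/no covariate for prior cerebral ischemia. Code it yes if any of the following holds:

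- a lesion on the baseline DW-MRI;
- an old infarct on the baseline FLAIR/T2 images, which are already acquired, as scored by the existing blinded readers;
- a history of cerebral embolism.

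Report the infarct estimate with and without this covariate, so that its influence is visible.

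The cost is one sentence in the analysis plan, one extra item on the reading form and one degree of freedom. No additional scan or visit is needed.
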